### Study procedures

#### Informed consent (IC) and baseline assessment

Participants must personally sign and date the latest approved version of the IC form before any study-specific procedures are performed. The IC will be signed at the beginning of the baseline visit (T0) at the research center. Written versions of the IC will be presented to the participants, where it is clearly stated that the participant is free to withdraw from the study at any time for any reason, and with no obligation to give the reason for withdrawal. After the IC is signed by the participant, the treating therapist or physician (TAU) is informed by the researcher regarding the RCT participation. In case of additional participation in the (f)MRI sub-study, there will be a separate IC and safety form (contraindications MRI) to be signed by the participant before the baseline scanning session is initiated.

#### Randomization and blinding

Once the IC is signed during the baseline visit (T0), randomization is performed by the RA carrying out the measurement. A web-based randomization program using a list of unique randomization codes with block randomization (ratio 1:1, mifepristone *N* = 79, placebo *N* = 79) is used. Randomization will be stratified for fMRI participation. This way, the fMRI subgroups are well balanced with mifepristone and placebo interventions. During the T0 visit, the randomization code and study medication prescription are sent to the hospital pharmacy for dispensing. The randomization codes are kept by the hospital pharmacy and the data management team of Amsterdam UMC, location VUmc, out of reach from the involved researchers until data collection is completed. If de-blinding of study medication is needed in case of Serious Adverse Events (SAEs) for urgent medical reasons, the pharmacy can be contacted by the researchers.

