#### Intervention

Participants will receive either mifepristone (1200 mg/day) or placebo for 7 consecutive days. Tablets are packaged in HDPE-bottles containing 28 tablets of 300 mg each or placebo. Placebo tablets are matched to mifepristone tablets in shape, smell and colour. Study medication is orally ingested in the morning during a meal, 4 tablets of mifepristone (total 1200 mg) or placebo. Study adherence is assessed by drug tablet return and mifepristone plasma levels at T1.

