### Statistical analyses

All randomized participants will be included in the analyses according to the intention-to-treat (ITT) principle. Primary and secondary outcomes will be assessed over time between groups using a linear mixed models (LMM) as it can account for missing data. The primary outcome is depressive symptom severity using the continuous outcome of the IDS-SR questionnaire completed 6 weeks after the start of the intervention (T2). Secondary outcomes are assessed throughout the study from 1 week (T1) to 6 months (T4) after the start of the intervention. All (primary and secondary) outcomes will also be stratified by low or high plasma mifepristone levels based on Block et al. 2018. The significance threshold is set at *p* = 0.05, with correction for multiple testing for secondary outcomes. Descriptive and biological factors will be examined as potential determinants of mifepristone’s treatment effects by studying moderation and mediation. Adverse side effects from the treatment are tested between groups with a 2-sample t-test. Data from the (f)MRI sub-sample will be pre-processed and analyzed using existing pipelines (fMRIPrep) and FSL (FMRIB Software Library) and is assessed in relation to depression severity and treatment condition.

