### Data management and quality assurance

Data will be collected and stored digitally using an electronic Case Report From (eCRF) in Castor EDC (a certified online data collection tool for medical research) or Survalyzer (during screening), with the exception of the signed IC and biological samples. Study data from questionnaires and clinical interviews in Castor EDC, collected hair, saliva and blood samples are stored, handled, and de-identified using the ID number. Only the local research team, the pharmacy staff, the data managers at Amsterdam UMC, location VUmc and the study monitor will have access to Castor EDC and the separate database that connects the ID study number to a person. Screening information is used to report the progress of inclusion according the CONSORT criteria that is needed for publishing (‘not meeting inclusion criteria’, ‘declined to participate’ or ‘other reasons’). The Clinical Monitoring Center (CMC) from the Amsterdam UMC will ensure that the study is adequately monitored during and after completion of data-collection.

Data will be stored 15 years upon completion of the study. For the collection and use of blood, saliva and hair samples for the current study, consent is needed from the participant. Blood samples will be stored at the central VUmc biobank in cryovials at -80 °C, and are stored for 15 years if the participant provided explicit consent. If the participant does not give consent for the biobank, blood samples will be destroyed within 5 years after data collection is completed, together with the saliva and hair samples. Saliva samples will be stored at the central VUmc laboratory and hair samples will be stored centrally at the study site (Amsterdam UMC, location VUmc) at room temperature.

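### The randomization codes may reach the researchers when data collection ends, a point that comes before the end of monitoring, instead of at database lock

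*Protocol article*

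**What the plan says.** Under Randomization and blinding, the protocol article names who holds the allocation: "The randomization codes are kept by the hospital pharmacy and the data management team of Amsterdam UMC, location VUmc". It then says how long the codes are withheld: they stay "out of reach from the involved researchers until data collection is completed". The one exception is an emergency route through the pharmacy: "If de-blinding of study medication is needed in case of Serious Adverse Events (SAEs) for urgent medical reasons". The article does not mention database lock, a blinded data review or a completed analysis plan as a condition for release.

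Two statements under Data management and quality assurance bear on this. The hospital's monitoring centre "will ensure that the study is adequately monitored during and after completion of data-collection". Access to the data is restricted, but the researchers are among those who have it: "Only the local research team, the pharmacy staff, the data managers at Amsterdam UMC, location VUmc and the study monitor will have access to Castor". This is the system that holds the questionnaire and interview data.

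The Intervention section adds: "Study adherence is assessed by drug tablet return and mifepristone plasma levels at T1".

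**The concern.** In a double-blind trial the blind should also cover the handling of the data, up to the moment when no value can change. The end of data collection is earlier than that. Between the last visit and lock, queries are answered, implausible values are corrected or set to missing, scans are pre-processed and quality-checked, and outstanding assays are run and read. Someone who knows the allocation can, without intending to, make these small decisions differently in the two arms. This trial has many secondary and mechanistic measures, and some of them need such decisions.

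The point is not that the article omits a detail. It chose a milestone for release and published it, and a later milestone would protect the trial better at almost no cost.

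**Working it through.** No calculation settles this point, so the check sets the statements side by side.

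1. **Release point.** Randomization and blinding sets the end of data collection. No other section of the article sets a later point.

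2. **Is that milestone the same as lock?** The article's own usage suggests not. Under Data management and quality assurance, monitoring runs both during and after completion of data collection, so study work continues beyond it. The same section lets samples without biobank consent be kept for up to 5 years after the milestone before they are destroyed. Material for assay may therefore still exist after the codes can be released. The article does not say that assays will be outstanding then.

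3. **Who could act on the data?** The local research team has access to Castor EDC. The article does not say that this access ends, or becomes read-only, when the codes are released.

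4. **What could be affected?** I take data collection to end with the last 6-month (T4) measurement, since T3 and T4 are scheduled study measurements. The article does not define it. On that reading:
   - Primary outcome: the IDS-SR at T2 is completed by the participant, and every value exists before release. Only query resolution remains, so the exposure is small.
   - Interview-based outcomes: the MINI-S interviews through T4 are finished before release. Only corrections remain.
   - Imaging: pre-processing and analysis (Statistical analyses) may follow the last visit.
   - Cortisol, inflammation and epigenetic measures: any assay or processing still outstanding would be exposed.

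5. **Effect on the stated design figures.** The Sample size section uses d = 0.50, two-sided α = 0.05, power 80% and 20% dropout. By the normal approximation, n per group = 2 × (1.960 + 0.842)² / 0.50² = 62.8, so 63. Then 63 / (1 − 0.20) = 78.75, so 79 per arm and 158 in total, as stated. The release date enters none of these terms, so moving it changes none of these figures.

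**The case against.** The best defence is that the phrase is shorthand. *Until* gives the period during which the codes are certainly withheld. It does not say that they are handed over the day after the last visit, and the authors may mean lock. Lock and cleaning procedures usually sit in a full protocol or data-management plan, which a journal article condenses. This stands as a limit: the text permits early release and does not show that it will happen. It does not remove the point, because the article names a specific milestone and elsewhere treats it as one after which work continues.

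A reader might infer three stronger things, and the article does not support them.

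- **That key definitions would still be open at unblinding.** They are fixed. Biological markers sets the plasma cut-off at 1637 ng/mL. Statistical analyses includes all randomized participants by intention to treat. Secondary outcomes defines remission at T2 as an IDS-SR score below 14 confirmed by MINI-S, and response as a 50% fall in the score.
- **That the multiplicity method and the moderators and mediators would be chosen with allocation known.** The article does not specify them, but an analysis plan that is not shown may do so before release. This point does not rely on them.
- **That T1 plasma levels already unblind the researchers.** A measurable drug level would point to active treatment. But the article does not say when the assays are run, who receives the results, or whether they enter the database during the trial. Frozen storage is compatible with a later batch assay. What remains is a conditional precaution.

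**Conclusion.** The point holds in a limited form. The published rule ends the researchers' blind at a milestone that precedes the end of monitoring, while the research team has database access. It therefore permits query resolution and the processing of remaining secondary, imaging and biomarker data with allocation known. The size of any resulting bias cannot be calculated from the article. It should be small for the self-reported primary outcome and is of more concern for data processed after the last visit.

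The conclusion rests on two assumptions: that completion of data collection means the last T4 measurement, and that no document outside the article sets a later release point. If a full protocol already ties release to lock, the sentence only needs to be aligned with it. This is a cheap improvement to the wording of the safeguard. It is not evidence that the blind has failed or will fail.

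**What to change.** In Randomization and blinding, replace the release point so that the codes stay with the pharmacy and data management *until the analysis plan is final and the database is locked*. Leave the emergency unblinding for serious adverse events as it is.

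As a precaution, add a data-management instruction: if T1 mifepristone plasma results become available before lock, the laboratory or data management holds them and releases them to the researchers under the same rule. Data management already holds the codes, so it would learn nothing new from them.

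The cost is one sentence and one instruction, and researchers wait until lock for the codes and for any plasma results held with them. Trial status reports that recruitment was still under way at publication, so the change could be made before the milestone was reached.

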#### Intervention

Participants will receive either mifepristone (1200 mg/day) or placebo for 7 consecutive days. Tablets are packaged in HDPE-bottles containing 28 tablets of 300 mg each or placebo. Placebo tablets are matched to mifepristone tablets in shape, smell and colour. Study medication is orally ingested in the morning during a meal, 4 tablets of mifepristone (total 1200 mg) or placebo. Study adherence is assessed by drug tablet return and mifepristone plasma levels at T1.

### Assessments, outcomes and instruments

#### Primary outcome

The primary outcome is depressive symptom severity as measured by the IDS-SR 6 weeks after the start of the intervention (T2). The IDS-SR is a questionnaire with high internal consistency and good concurrent validity [45].

#### Secondary outcomes

MDD remission (< 14 on IDS-SR, confirmed with the MINI-S), 6 weeks (T2) after the start of the intervention.Short-term depressive symptom severity (IDS-SR) and MDD remission (MINI-S), 1 week (T1) after the start of the intervention.Long-term depressive symptom severity (IDS-SR) and MDD remission (MINI-S), 12 weeks (T3) and 6 months (T4) after the start of the intervention.Treatment response (50% decrease in IDS-SR score) at all post-intervention time-pointsDisability (WHO Disability Schedule 2.0; WHO-DAS II) [46], at all post-intervention time-points.Sleep (Pittsburgh Sleep Quality Index; PSQI) [47], at all post-intervention time-points.Subjective stress (Perceived Stress Scale; PSS) [48], at all post-intervention time-points.Anxiety symptoms (Beck Anxiety Inventory; BAI) [49], at all post-intervention time-points.

### Descriptive variables

The following descriptive variables and potential moderators/mediators will be assessed in order to thoroughly describe the study sample.Age, sex, smoking, BMI, physical activity (International Physical Activity Questionnaire; IPAQ) [50], alcohol use (Alcohol Use Disorders Identification Test; AUDIT) [51].Current treatment (type, duration and frequency; self-composed questionnaire TAU)Adverse side effects of study medication (self-composed questionnaire)Characteristics (e.g. type, chronicity) of CT (CTQ-SF and Maltreatment and Abuse Chronology of Exposure; MACE) [52]Resilience (Connor Davidson Resilience Scale; CD-RISC2) [53]Coping style (COPE-16) [54]Personality traits (NEO Five-Factor Inventory; NEO-FFI) [55]Comorbid PTSD/ASD diagnosis (non-primary diagnosis) (MINI-S) [56]Life events (List of Threatening Experiences; LTE) [57]Social support (Social Support List; SSL) [58]Suicidal ideation and behaviour (Columbia-Suicide Severity Rating Scale; C-SSRS) [59].This is used within a suicide prevention protocol in case participants show a risk regarding suicidality when they answer positively on the suicidality item of the MINI-S, which is assessed at every study time-point.

### Biological markers

Various stress related biomarkers are assessed pre- and post-intervention to better understand the underlying mechanism of a clinical response to mifepristone treatment (see Table 2):Saliva samples are taken at home pre- and post-intervention (T0, T1, T2) to assess the Cortisol Awakening Response (CAR), directly at awakening, at 30 min, and 45 min after awakening [60]. Also, one evening sample between 21-22 pm is collected, as ultradian rhythmicity shows lowest variability in the evening, resulting in reliable cortisol assessments [61].Hair samples are collected pre- and post-intervention (T0, T2) to retrospectively assess cumulative cortisol levels, as it is a good reflection of a more chronic cortisol exposure [62].Blood samples are collected pre- and post-intervention (T0, T1, T2) for various biomarkers:◦ Mifepristone blood plasma levels are assessed from T1 blood samples, 1 day after the last study medication. Based on previous clinical trials with a 7-day mifepristone treatment, high plasma levels (HPL; ≥ 1637 ng/mL) are expected to be associated with a higher clinical response compared to low plasma levels (< 1637 ng/mL). Due to inter-individual variability in mifepristone metabolization, 65% of participants are expected to reach HPL with a 1200 mg daily dose [39].◦ Inflammatory markers like C-reactive protein (CRP), Tumor Necrosis Factor-alpha (TNF-α) and Interleukin-6 (IL-6) are assessed as these have been found to be elevated in patients with MDD or CT [63].◦ Epigenetic regulation is assessed from somatic white blood cells through genome-wide microarrays, as preclinical findings indicated mifepristone could alter DNA expression and thereby reverse the negative effects of long term GR overactivation [64].

**Table 2 Tab2:** Overview of RESET-medication measurements per study time-point

**Construct**	**Instrument**	**Method**	**Screening**	**T0**	**T1**	**T2**	**T3**	**T4**
Depression symptom severity	IDS-SR	SR	X	X	X	X	X	X
Childhood trauma	CTQ-SF	SR	X					
MDD diagnosis	MINI-S	Int		X	X	X	X	X
Suicidality	C-SSRS	Int		^b^	^b^	^b^	^b^	^b^
Anxiety symptoms	BAI	SR		X	X	X	X	X
Disability	WHODAS-II	SR		X	X	X	X	X
Sleep duration	ISI	SR		X	X	X	X	X
Perceived stress	PSS	SR		X	X	X	X	X
Stressful life events	LTE	SR		X		X	X	X
Social support	SSL	SR		X	X	X	X	X
Medication adherence-TAU	MARS-5	SR		X	X	X	X	X
Medication adherence-RCT	Pill count	Int			X			
Adverse side effects	SC	SR			X^c^			
Demographics	SC	Int		X				
Past/current smoking	SC	SR		X				
Physical activity	IPAQ	SR		X				
Alcohol use	AUDIT	SR		X				
Drug use	SC	SR		X				
PTSD symptoms	MINI-S	Int		X				
Current/previous TAU	SC	Int		X				X
Resilience	CD-RISC2	SR		X				
CT characteristics	MACE	SR		X				
Coping style	COPE-16	SR		X				
Personality traits	NEO-FFI	SR		X				
Contraindications mifepristone	SC	Int	X	X				
Pregnancy test	Urine	BM		X				
Cortisol	Hair Saliva	BM BM		X X	X	X X		
Inflammation, epigenetics, mifepristone plasma levels	Blood	BM		X	X	X		
fMRI sub-study^a^: Stress-related biological measures	Structural MRI, resting-state fMRI task-based fMRI; Saliva Heart-rate	BM BM BM BM BM		X X X X X		X X X X X		
fMRI sub-study: Subjective stress measures	PANAS STAI-S VAS DARS	SR SR SR SR		X X X X		X X X X		

*T0* Baseline, *T1* 1 week after start study medication, *T2* 6 weeks after start study medication, *T3* 12 weeks after start study medication, *T4* 6 months after start study medication, *TAU* treatment as usual, *SR* Self-Report, *Int* Interview by researcher, *BM* Biological measure, *IDS-SR* Inventory of depressive symptomatology-self rated, *MINI-S* Mini International Neuropsychiatric Interview-Simplified, *CTQ-SF* Childhood Trauma Questionnaire – Short Form, *C-SSRS* Columbia-Suicide Severity Rating Scale, *BAI* Beck Anxiety Inventory, *WHODAS-II* WHO Disability Schedule-II, *ISI* Insomnia Severity Scale, *PSS* Perceived Stress Scale, *LTE* List of Threatening Experiences, *SSL* Social Support List, *MARS-5* Medication Adherence Report Scale, *SC* self-composed questionnaire, *IPAQ* International Physical Activity Questionnaire, *AUDIT* Alcohol Use Disorders Identification Test, *CD-RISC2* 2-item Connor-Davidson Resilience Scale, *MACE* Maltreatment and Abuse Chronology of Exposure questionnaire, *COPE-16* Coping Orientation to Problems Experienced*, NEO-FFI* NEO Five-Factor Inventory, *fMRI* functional Magnetic Resonance Imaging

^a^only in fMRI sub-group

^b^only assessed if patient shows risk regarding suicidality

^c^repeated 2 weeks after T1

### Neuro-imaging

In order to test for potential neurobiological effects of mifepristone treatment, a (f)MRI sub-study will be conducted in a sub-group of *N* = 80 patients (*N* = 40 per group), at baseline (T0) and repeated at post-intervention (T2). Within each visit (T0, T2) there are two (f)MRI sessions which will be conducted after the TSST in order to assess the acute (0–40 min) and recovery (60–100 min) phases of stress system dynamics in response to a psychosocial stressor. The scanning procedure consists of anatomical scans (T1, Diffusion Tensor Imaging; DTI), functional resting-state, and two commonly used fMRI tasks: 1) N-back working memory task [65] where participants are presented a series of stimuli one-by-one and are asked to decide for each stimulus whether it matches the one displayed n (1,2, 3, etc.) trials ago. 2) Situation-focused volitional reappraisal task [66] where participants are presented with positive, negative or neutral pictures and are asked to either positively reinterpret the displayed situation (situation-focused volitional reappraisal) or to attend the picture without manipulating the emotional response to it (control condition). After each picture, participants were asked to rate their emotional state using a Self-Assessment Manikin for valence (SAM) [67], which served as the outcome measure. Pictures are selected from the International Affective Picture System (IAPS) based on normative ratings in valence and arousal [68].

For all functional scans T2*-weighted echo planar images (EPIs), sensitive to blood oxygenation level-dependent (BOLD) contrast will be obtained, covering the entire brain. Stress system dynamics in response to the TSST will also be assessed on the level of endocrine responses (salivary cortisol and alpha-amylase), psychophysiology (heart rate) and behaviour (in fMRI tasks). All task stimuli are presented using the stimulus presenter software Presentation (Neurobehavioral Systems, Albany, CA). Scanning protocols are identical for baseline and post-intervention assessments and are conducted at a 3 Tesla scanner at the Spinoza Centre for neuroimaging, Amsterdam, the Netherlands.

### Statistical analyses

All randomized participants will be included in the analyses according to the intention-to-treat (ITT) principle. Primary and secondary outcomes will be assessed over time between groups using a linear mixed models (LMM) as it can account for missing data. The primary outcome is depressive symptom severity using the continuous outcome of the IDS-SR questionnaire completed 6 weeks after the start of the intervention (T2). Secondary outcomes are assessed throughout the study from 1 week (T1) to 6 months (T4) after the start of the intervention. All (primary and secondary) outcomes will also be stratified by low or high plasma mifepristone levels based on Block et al. 2018. The significance threshold is set at *p* = 0.05, with correction for multiple testing for secondary outcomes. Descriptive and biological factors will be examined as potential determinants of mifepristone’s treatment effects by studying moderation and mediation. Adverse side effects from the treatment are tested between groups with a 2-sample t-test. Data from the (f)MRI sub-sample will be pre-processed and analyzed using existing pipelines (fMRIPrep) and FSL (FMRIB Software Library) and is assessed in relation to depression severity and treatment condition.

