In line with the notion of an overactivated HPA-axis during, and possibly after stress in early life, treatment with a GR antagonist emerges as a promising strategy from the animal literature [28–31]. In several studies, administration of the GR-antagonist mifepristone in adolescent rodents exposed to early life stress reversed increased freezing behaviour at adult age [28] and normalized open-field behaviour and corticosterone levels when administered at adult age [31]. Mifepristone also reversed changes in social behaviour in animals stressed during adolescence [30]. Thus, in rodents, the GR antagonist mifepristone seems to be able to counteract long-term GR overactivation following early life stress. In humans, such effects of GR antagonism have not been examined. Nevertheless, the GR antagonist mifepristone has been widely used for decades to treat Cushing’s syndrome [32]. Based on beneficial effects on psychiatric symptoms observed in Cushing’s disease, mifepristone has also been investigated for psychotic depression (7-day mifepristone regimen 300–1200 mg/day) [33–38]. A combined analysis of five RCTs showed an overall significant effect of mifepristone (*N* = 793) vs. placebo (*N* = 595) in reducing psychotic symptoms in psychotic depression, but significantly more so in patients with high plasma mifepristone levels after 7 days (d = 0.3) compared to low plasma levels (d = 0.05) [39]. From these studies, a 7-day mifepristone treatment is known to be generally well-tolerated and adverse events (AEs) were not significantly different compared to placebo treatment.

The REStoring mood after Early life Trauma (RESET) study is a double-blind, placebo-controlled, randomized trial that tests the hypothesis whether a 7-day treatment using the GR antagonist mifepristone (1200 mg) improves depression in patients with moderate to severe MDD and CT.

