### Adverse event reporting

Adverse events (AEs) are defined as any undesirable experience occurring to a participant during the study, whether or not considered related to the investigational product or trial procedure. AEs are actively inquired during post-intervention visits. Additionally, a side-effects questionnaire is filled out by participants at T1 and is repeated 2 weeks later. These time points were chosen based on mifepristone's half-life of 85 h at steady-state with 600 mg/day. Participants, who experience severe side effects, are allowed to reduce the daily dose to 600 mg for the rest of the 7 day period, if deemed medically safe. All serious adverse event (SAE) related to (mental) health excesses or death are reported to the accredited Medical Research Ethical Committee (MREC) that approved the protocol according to its requirements.

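### Remission and response are yes/no outcomes but are assigned to a linear mixed model; if their rates rise over visits and one variance is pooled, the visit-specific tests are miscalibrated

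*Protocol article*

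**What the plan says.** The Statistical analyses section of the protocol article names one model for efficacy: "Primary and secondary outcomes will be assessed over time between groups using a linear mixed models (LMM) as it can account for missing data". It makes no exception for binary outcomes and gives no covariance structure.

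The Secondary outcomes section lists "MDD remission (< 14 on IDS-SR, confirmed with the MINI-S), 6 weeks (T2) after the start of the intervention". It adds remission at T1, T3 and T4, and treatment response (a halving of the IDS-SR score) at every visit after the intervention. Both are yes/no per patient and visit.

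For tolerability the plan states: "Adverse side effects from the treatment are tested between groups with a 2-sample t-test". The Descriptive variables section gives the source as "Adverse side effects of study medication (self-composed questionnaire"), and the Adverse event reporting section says that "a side-effects questionnaire is filled out by participants at T1 and is repeated 2 weeks later". Neither says whether the items are yes/no, counts or severity grades.

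No expected rate is given for remission, response or side effects. The nearest statement, in the Background, is that in earlier studies "adverse events (AEs) were not significantly different compared to placebo treatment".

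**The concern.** A standard linear mixed model estimates one residual variance from all visits and uses it for the treatment contrast at each visit. For a yes/no outcome the true variance at a visit is p(1-p), so it grows as the rate rises towards one half. If few patients remit early and more do so later, the pooled variance is too large at the first visit and too small at the last. The early test then has almost no chance of rejecting, and the late test rejects too often.

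Rising rates are plausible here. Patients enter with an IDS-SR of 26 or more and remission needs a score below 14. T1 is at one week and T4 at six months, and usual care may be continued or started during the study. Remission and response at T3 and T4 also bear on the claim of a disease-modifying effect. The planned multiplicity correction for secondary outcomes does not repair p-values that are miscalibrated before correction.

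Side effects raise a smaller issue: the plan fixes a comparison of means without saying what quantity is averaged.

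**Working it through.** **Inputs from the article.** Primary outcome: d = 0.50, two-sided α = 0.05, power 80%. Then n = 2(1.960 + 0.842)²/0.50² = 62.8, so 63 per arm. With 20% dropout, 63/0.80 = 78.75, so 79 per arm and 158 in total. The stated sample size reproduces and supplies the arm sizes below. The article has no figure of its own for remission, response or side effects.

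**Assumptions.** Null rates at T1 to T4 (several sets), no treatment effect, complete data, and a random-intercept model with one residual variance.

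**Step 1: formula.** The true variance at visit k is v_k = p_k(1-p_k). The pooled model uses v̄, the mean of the four. The ratio of true to model standard error is r_k = √(v_k/v̄), and the actual two-sided error is 2Φ(-1.96/r_k). The arm size cancels.

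**Step 2: rates of 2/8/15/20%.** The v_k are 0.0196, 0.0736, 0.1275 and 0.1600, with mean 0.0952.

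| Visit | r_k | Actual error |
|---|---|---|
| T1 | 0.454 | 0.000 |
| T2 | 0.879 | 0.026 |
| T3 | 1.157 | 0.090 |
| T4 | 1.297 | 0.131 |

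**Step 3: other assumed rates.**

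| Rates T1 to T4 | T1 | T2 | T3 | T4 |
|---|---|---|---|---|
| 2/5/10/15% | 0.000 | 0.016 | 0.081 | 0.143 |
| 5/10/15/20% | 0.003 | 0.033 | 0.074 | 0.110 |
| 5/15/25/30% | 0.001 | 0.038 | 0.087 | 0.106 |
| 10/20/30/35% | 0.007 | 0.042 | 0.076 | 0.089 |
| 15/20/25/30% | 0.023 | 0.043 | 0.061 | 0.077 |
| flat 15% | 0.050 | 0.050 | 0.050 | 0.050 |

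**Step 4: simulation.** I drew four correlated binary visits (latent correlation 0.5, 20,000 runs, pooled variance). For 2/8/15/20% and 63 per arm, rejection was 0.000, 0.026, 0.091 and 0.131. With 79 per arm it was 0.000, 0.027, 0.089 and 0.131. Random-intercept models fitted by REML to the same rates (63 per arm, 400 runs, Monte Carlo SE at most about 0.017) gave 0.000, 0.028, 0.075 and 0.135. With a separate variance at each visit, rejection lay between about 0.02 and 0.056 in every scenario, and it was lowest where events were very sparse.

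**Step 5: t-test on yes/no side effects.** Enumerating every 2×2 table with 79 per arm gives the true size at nominal 0.05:

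| Common rate | t-test | Chi-square, uncorrected | Fisher |
|---|---|---|---|
| 1% | 0.008 | 0.008 | 0.000 |
| 2% | 0.031 | 0.031 | 0.002 |
| 5% | 0.042 | 0.050 | 0.016 |
| 10% | 0.049 | 0.052 | 0.028 |
| 20% | 0.050 | 0.052 | 0.032 |
| 30% | 0.051 | 0.051 | 0.033 |

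Over rates from 0.5% to 50% the t-test peaks at 0.052 (79 per arm) or 0.054 (63 per arm). For 4/79 against 0/79, the t-test and chi-square both give p = 0.043 and Fisher gives 0.120. For 5/79 against 0/79, the values are 0.023, 0.023 and 0.059.

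**The case against.** The strongest reply on efficacy is that the fault lies in a covariance option which the article never states. A linear mixed model with visit-specific variances holds its level (Step 4), flat rates cause no problem, and the size of the error depends on rates that the article does not give. This stands, and it rules out saying that the standard error is wrong at every visit. At T2, where the first-listed remission outcome sits, the pooled model is conservative under all the rising-rate sets above (1.6% to 4.3%). A separate simulation of the T2 contrast with other assumed rates gave 3% to 5%.

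A second reply is that a condensed article may leave the model for binary outcomes to the full protocol or analysis plan. That is fair for detail that is absent. Here, though, the text positively assigns one linear model to every secondary outcome. A fuller document may already correct this, in which case only the article's wording is at fault.

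A third reply is that the mixed model was chosen to cope with missing data. A logistic mixed model keeps that advantage.

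On side effects, a reader might infer that a t-test on rare yes/no events is anti-conservative and would raise false safety signals. The article does not say that the items are yes/no, and a t-test is ordinary for a sum score. Even for yes/no items, Step 5 shows a test that is conservative at low rates and never far above 5%. The gap to Fisher in sparse tables mainly reflects Fisher's conservatism, which costs power to detect harm: for 5% against 15% with 79 per arm, 47% against 57% for the t-test.

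**Conclusion.** The point holds for remission and response, conditionally. If one residual variance is pooled and rates rise over visits, the T1 tests run at about 0% to 2% and the T4 tests at about 8% to 14%, against a nominal 5%. If rates are flat, or the variance is allowed to differ by visit, there is no material inflation. The figures rest on assumed rates, complete data and an assumed covariance form.

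Apart from error rates, a linear model can give fitted probabilities outside 0 to 1.

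For side effects the point is one of clarity and reporting: the quantity compared is not stated, and a mean is a poor summary of how many patients were affected. It would also be wrong to say that the trial expects low event rates, since the article gives none.

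The matter touches secondary and safety outcomes only. The IDS-SR at T2 is continuous, so the primary analysis and the sample size are unaffected. It is worth correcting because the method can be named now at almost no cost.

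**What to change.** Limit the linear mixed model to the continuous scales. State that remission and response are analysed with a logistic mixed model or a logistic GEE, with arm by visit, baseline IDS-SR and the fMRI stratum, reported as risk differences with 95% CIs. If GEE is chosen, add weighting or multiple imputation so that missing data are handled no less well than under the mixed model. Name a fallback for visits with very few events, such as a risk difference with an exact or score interval: at an assumed 2% with 63 per arm, only 0.02 × 63 = 1.3 remissions per arm are expected, and a logistic model may not converge.

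For side effects, state the scale of the questionnaire. For yes/no items, report the number of patients affected per arm with a risk difference and 95% CI. Keep the t-test only for a sum score, if there is one.

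The cost is a few sentences of analysis text and no new data.
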